#### Sample size

The sample size was calculated based on the primary outcome.

There were very few studies available with outcome data matching the age and morbidity of the AF SPICE trial. Very few studies on patients with an index stroke incident were available; in particular, there was a lack of data regarding patients with recent strokes and AF without OAC treatment. For this, we have made estimations and extrapolations using the very few available studies on patients with AF without OAC treatment. In particular, extrapolations have been made with regard to age since most available studies have included patients considerably younger than what is expected in AF SPICE. A list of studies used in sample size estimations is available in online supplemental appendix.

10.1136/bmjopen-2023-073470.supp1Supplementary data

For the estimations of AF detection proportions, available studies on short-term (48±24 hours) ECG recordings following stroke and corresponding studies on long-term (14 days) recordings were used. As with the outcome data, no studies with similar populations and ECG recording durations were available. Furthermore, the AF detection/incidence was estimated for the entire follow-up for both arms, reflecting the additional detection within standard care after the index event, thereby reflecting the actual risk exposure in both arms during follow-up. A list of the AF detection studies available for this estimation is reported in online supplemental appendix.

The assumptions for the sample size calculation are reported in table 2. The complete sample size calculation is provided in the appendix. For the yearly risk of the composite endpoint, we estimate 17% in patients with AF and no OAC treatment, 7.3% in patients with AF and OAC treatment and 5% risk in patients without AF. We further estimate an AF detection proportion of 6% in the control group and 19% after two ECG recordings in the intervention group, and 13% with untreated AF in the control group, resulting in a sample size of 2718 for 3 years of fixed follow-up time after inclusion. Adding 20% for participant dropouts and treatment discontinuation, a total sample size of 3262 is needed, corresponding to 1631 in each arm based on 3 years of follow-up, 80% power and a double-sided significance level of 5%. The study is powered to detect a 9% reduction in the composite endpoint in the group with extended ECG screening.

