**Table 2 T2:** Event rates and AF detection rates used in sample size calculation

Endpoint* risk in patients with AF and OAC treatment	7.3%
Endpoint risk in patients with AF and no OAC treatment	17%
Endpoint risk in patients without AF	5%
AF detection proportion in standard arm†	6%
AF detection proportion in intervention arm†	19%

*Endpoint including recurrent stroke, all-cause mortality and intracerebral bleeding.

†Including AF detection during follow-up.

AF, atrial fibrillation; OAC, oral anticoagulation.

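### The printed sample-size inputs do not give 2718 patients for 80% power over three years; they need about 3,230 to 6,170 analysed patients

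*Protocol article*

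**What the plan says.** The Sample size section gives the yearly risk of the composite endpoint as "17% in patients with AF and no OAC treatment, 7.3% in patients with AF and OAC treatment and 5% risk in patients without AF". It gives an "AF detection proportion of 6% in the control group and 19% after two ECG recordings in the intervention group", with a further 13% of controls having untreated AF. Table 2 repeats the three risks and the two detection proportions (for example the row "AF detection proportion in intervention arm", 19%).

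These inputs are presented as "resulting in a sample size of 2718 for 3 years of fixed follow-up time after inclusion". The figure is raised by 20% for dropout and treatment discontinuation to 3262, "corresponding to 1631 in each arm based on 3 years of follow-up, 80% power and a double-sided significance level of 5"%. The section adds that the complete calculation is in an appendix.

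Elsewhere, the Allocation section sets 1:1 randomisation, Statistical methods names the log-rank test as the primary test, and the Primary endpoint section treats 36 months as a minimum follow-up.

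**The concern.** The article prints enough to rebuild the calculation: a risk for each AF/treatment group, the share of each group in each arm, the follow-up, the error level and the power. A reader who does so gets a larger number than 2718 however the yearly risks are converted.

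This is the power statement for the primary superiority test. If the printed inputs are the intended ones, the chance of missing the assumed effect over three years is well above the stated 20%: about 27-54% at 2718. If the inputs are not the intended ones, the article misreports the assumptions against which the result will be judged.

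**Working it through.** **Inputs (Sample size section and Table 2).** Yearly risks: AF without OAC 17%, AF with OAC 7.3%, no AF 5%. Control arm: 6% detected AF, 13% untreated AF, leaving 81% without AF. Intervention arm: 19% detected AF, leaving 81%. Two-sided 5%, 80% power, 3 years, 1:1.

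**Assumption.** All detected AF is treated and the intervention arm has no untreated AF. The article does not say this outright, but 6 + 13 = 19 implies it. Leaving some intervention patients with untreated AF would lower power further.

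**Yearly risk per arm.**
- Control: 0.06 × 7.3 + 0.13 × 17 + 0.81 × 5 = 6.698%
- Intervention: 0.19 × 7.3 + 0.81 × 5 = 5.437%
- Ratio: 5.437 / 6.698 = 0.812

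**Formulas.** With 3-year risks p1 and p2: HR = ln(1 − p2)/ln(1 − p1). Events (Schoenfeld) = 4 × (1.960 + 0.842)² / (ln HR)². N = events / mean risk. Power = Φ(|ln HR| × √events / 2 − 1.960). The two-proportion formula was run alongside.

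**Worked example, most favourable (linear) reading.** p1 = 3 × 6.698 = 20.09%; p2 = 3 × 5.437 = 16.31%; mean 18.20%. HR = 0.794. Events = 31.40 / 0.0533 = 589. N = 589 / 0.1820, about 3,234 (two-proportion formula: 3,266). At 2718 the expected events are 2718 × 0.1820 = 495, and power is Φ(0.231 × 22.2 / 2 − 1.960) = 73%.

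**All readings, 3 years, two-sided 5%.**

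| Conversion | 3-year risks | HR | Events for 80% | N for 80% | Power at 2718 | Power at 3262 |
|---|---|---|---|---|---|---|
| Linear, 3 × yearly risk | 20.1% v 16.3% | 0.794 | 589 | 3,234-3,266 | 73% | 80% |
| Subgroup hazards averaged within arm | 19.0% v 15.5% | 0.796 | 601 | 3,486-3,518 | 69-70% | 77% |
| Arm yearly risk compounded | 18.8% v 15.4% | 0.806 | 678 | 3,961-3,994 | 64% | 72% |
| Arm yearly rate as constant hazard | 18.2% v 15.1% | 0.812 | 722 | 4,340-4,374 | 60% | 68% |
| Each subgroup compounded, then mixed | 18.3% v 15.4% | 0.826 | 864 | 5,119-5,156 | 53% | 61% |
| Each subgroup rate as hazard, then mixed | 17.7% v 15.0% | 0.838 | 1,002 | 6,132-6,172 | 46% | 53% |

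Simulated log-rank tests for the compounded-subgroup reading gave 54% at 2718 and 61% at 3262, in line with the formula.

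**The plan's own figure is not reproduced.** Expected events at 2718 are only about 444 to 495. Near-matches exist, but each changes a stated input. Linear risks with a one-sided 5% test and continuity correction give 2676. Linear risks over 3.5 years give 2694. Linear risks with 13% rather than 19% treated AF in the intervention arm give 2724 with continuity correction. Nothing shows that any of these was used.

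**The 20% addition** is reproduced: 2718 × 1.2 = 3262. The linear reading needs 3,234-3,266 patients before any loss, which is already the inflated total.

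**The case against.** Three objections deserve weight.

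*The calculation is in an appendix not at hand.* It may use further inputs; the article says that AF detection was estimated over the whole follow-up, so exposure could vary with time. This stands as a limit on the claim: one cannot say that the sample size itself was miscalculated, only that the inputs printed as producing it do not. It does not remove the discrepancy, because the article presents those inputs as resulting in 2718.

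*Follow-up may exceed three years.* The Primary endpoint section sets 36 months as a minimum, and Recruitment gives 3 years of inclusion. With uniform accrual and a common register cut-off 36 months after the last inclusion (an assumption), mean follow-up would be about 4.5 years. Using 4.5 years for everyone, power at 2718 / 3262 becomes about 91% / 95% (linear), 84% / 90% (averaged hazards), 79% / 86% (compounded), 76% / 83% (constant hazard), 60% / 68% (subgroups compounded) and 53% / 61% (subgroup hazards). A reader might infer from the three-year figures that the trial lacks 80% power as it will be run. The documents do not support that; it depends on the cut-off and the conversion. But the objection does not rescue the printed figure, which is stated for three years of fixed follow-up.

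*2718 is the pessimistic denominator.* Outcomes come from national registers, and patients who do not complete the ECG protocol stay in the analysis, so loss may be well below 20%. That is fair, and is why power at 3262 is shown. Part of the allowance is for treatment discontinuation, however, which dilutes the effect rather than removing patients, so 3262 is the optimistic end.

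**Conclusion.** The point holds for the printed figures. With the inputs in the Sample size section and Table 2, all detected AF treated and no untreated AF in the intervention arm, none of six conversions gives 2718 for "80% power and a double-sided significance level of 5"% over three fixed years. The required number is about 3,230 to 6,170 analysed patients, that is 19% to 127% above 2718 (3,230 / 2718 = 1.19; 6,170 / 2718 = 2.27). Power is about 46-73% at 2718 and 53-80% at 3262. The 80% is reached only with the linear conversion and every randomised patient analysed without loss or dilution.

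Two stronger readings should be avoided. One is that the inputs and the sample size cannot both be right under any calculation; the unseen appendix rules out that certainty. The other is that the trial should be run to 722 events; that number belongs to the constant-hazard reading alone, and the readings range from 589 to about 1,000.

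**What to change.** In the Sample size section:

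1. State how yearly risks were turned into 3-year risks, which test formula was used, and what treatment coverage was assumed for detected AF in each arm.
2. If a printed input is wrong, correct it in the text and in Table 2. If the inputs are right, restate the power at both 2718 and 3262 under the stated conversion, or give the effect detectable with 80% power at 2718 in three years: a hazard ratio of roughly 0.77 (0.76 to 0.78 across the readings above).
3. Reconcile the fixed three years with the minimum of 36 months in the Primary endpoint section. If longer register follow-up is meant to supply the power, say so, name the cut-off and compute the power for it. An event-driven analysis is a design option, not something this discrepancy requires. If it is chosen, the event target must follow from the stated conversion.
4. Bring the closing statement of a 9% reduction into line. The inputs imply about 15-19% relative, or 2.6 to 3.8 percentage points absolute, over three years.

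The cost is a rewording of one section and a less favourable power statement. It needs no extra patients or visits; a later register extraction would be needed only if longer follow-up is adopted.

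### The stated 9% detectable reduction contradicts the sample-size inputs, which imply about 19% on yearly risk; as a relative effect, 9% has only about 20-22% log-rank power

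*Protocol article*

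**What the plan says.** The Sample size section introduces its three event risks with "For the yearly risk of the composite endpoint". The highest of the three is for untreated AF: "we estimate 17% in patients with AF and no OAC treatment". The other two are 7.3% for treated AF and 5% where there is no AF. It assumes that AF is detected in 6% of the control arm and 19% of the intervention arm, and that a further 13% of control patients have untreated AF. Table 2 repeats the three risks and the two detection proportions (for example the row "Endpoint risk in patients with AF and no OAC treatment").

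From these the section reports 2718 patients for 3 years of fixed follow-up. It adds 20% to reach 3262 (1631 per arm), "based on 3 years of follow-up, 80% power" and a two-sided 5% level. The closing sentence is "The study is powered to detect a 9% reduction in the composite endpoint in the group with extended ECG screening". It does not say whether the 9% is relative or absolute, or yearly or cumulative. The complete calculation is said to be in an appendix. Statistical methods names the log-rank test as the primary analysis.

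**The concern.** Inputs, sample size, power and detectable effect are tied together: once three are fixed, the fourth follows. Here all four are printed in one paragraph, and the effect does not look like what the others would produce. Moving 13% of patients from a 17% yearly risk to 7.3% should lower the arm's risk by about 0.13 × 9.7 = 1.26 points a year. Against a control risk between 6% and 7%, that is nearer a fifth than a tenth.

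The detectable effect is what funders, the DSMB and later readers use to judge how sensitive the trial is. If it is quoted at about half its real size, the trial appears able to find small benefits that it would usually miss.

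**Working it through.** **Inputs** (Sample size section and Table 2): yearly risks of 17%, 7.3% and 5%; control mix of 81% no AF, 6% treated AF and 13% untreated AF; intervention mix of 81% no AF and 19% treated AF; two-sided 5%; 80% power; 3 years; 1:1 allocation. The 81% is 100 − 19, with the same total AF in both arms (6 + 13 = 19).

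**Step 1. The plan's own figures.** 2718 × 1.2 = 3261.6, so the step from 2718 to 3262 reproduces. The 2718 itself does not (step 3).

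**Step 2. Implied yearly effect.**
- Control: 0.81 × 5 + 0.06 × 7.3 + 0.13 × 17 = 6.698%.
- Intervention: 0.81 × 5 + 0.19 × 7.3 = 5.437%.
- Difference 1.26 points; relative reduction 1 − 5.437/6.698 = 18.8%.

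**Step 3. Implied 3-year effect, and power for it.** The article does not say how yearly risk becomes 3-year risk, so four conversions are shown. HR = ln(1 − p_int)/ln(1 − p_con). Events for 80% power = 4 × (1.960 + 0.842)²/(ln HR)² = 4 × 7.849/(ln HR)². N = events divided by the mean event probability. Power = Φ(|ln HR| × √events / 2 − 1.96).

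| Conversion | Control | Interv. | Relative | Points | HR | N for 80% | Power, 2718 | Power, 3262 |
|---|---|---|---|---|---|---|---|---|
| 3 × yearly | 20.1% | 16.3% | 18.8% | 3.8 | 0.79 | 3,230 | 73% | 80% |
| Arm average compounded | 18.8% | 15.4% | 17.8% | 3.3 | 0.81 | 3,960 | 64% | 72% |
| Arm average, exponential | 18.2% | 15.0% | 17.3% | 3.2 | 0.81 | 4,340 | 60% | 68% |
| Each subgroup compounded | 18.3% | 15.4% | 15.9% | 2.9 | 0.83 | 5,120 | 53% | 61% |

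N is rounded to the nearest 10. Two-proportion formulas give nearly the same values (3,264 and 3,994 for the first two rows). Applying the exponential within each subgroup goes slightly lower still: about 15% relative, 2.6 points and 46% power at 2718. No row gives 9%, and no row gives 2718 at 80% power.

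**Step 4. 9% read as relative.**
- Log-rank, HR 0.91: ln 0.91 = −0.0943, and 4 × 7.849/0.0943² ≈ 3,530 events. That exceeds the 3262 patients in the trial.
- Power at 3262, compounded control risk of 18.8%: the intervention risk is 1 − 0.812^0.91 = 17.2% and the mean 18.0%, so about 588 events. Φ(0.0943 × √588/2 − 1.96) = Φ(−0.82) = 21%. Across the four conversions this is 20-22%; by two proportions, 23-26%.
- N for 80% power: about 14,900 (two proportions, 3 × yearly) to about 20,200 (log-rank, exponential).

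**Step 5. 9% read as absolute.** The largest 3-year difference in the table is 3.8 points, and 9/3.8 = 2.4. A true 9-point difference would need only about 450-510 patients, so it cannot be the basis for 2718 either.

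**The case against.** Four points can be made for the plan.

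*A reader might infer that the sentence is false under every reading.* The documents do not support that. A 9-point absolute reduction is literally detectable with 3262 patients; the trouble is that the inputs cannot produce it. A yearly relative figure close to 9% also appears if control is taken to have 13% AF in total (6% treated, 7% untreated): 0.87 × 5 + 0.06 × 7.3 + 0.07 × 17 = 5.978%, and 1 − 5.437/5.978 = 9.05%. That reading contradicts the stated 13% untreated AF, gives randomised arms different AF prevalence, and would need about 17,000 patients or more. It may explain the number, but it does not make the trial powered for it.

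*It may be a dropped digit.* With 3 × yearly risk, 18.8% rounds to 19%, and the two-proportion N is 3,264, close to 3262. This is possible but cannot be confirmed, and 3262 already contains the 20% addition. It does matter for interpretation: the 15,000-20,000 patients describe an effect that the investigators may never have planned for. They do not show that the trial is short by that many.

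*The appendix holds the full calculation.* It is not shown and may use further assumptions. It could explain where 9% or 2718 came from, but it cannot make the printed inputs, N, power and effect all true together.

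*The harm is limited.* A reader might infer that a neutral result would be taken to exclude benefits of 9% or more. The plan reports hazard ratios with 95% confidence intervals, and those, not the planning sentence, settle what is excluded. This stands; the damage is to how the design is understood. Longer follow-up does not rescue the figure: if patients were followed for 3 to 6 years (an assumption drawn from the minimum of 36 months and 3 years of inclusion), power for HR 0.91 is still only about 27%.

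**Conclusion.** The 9% is wrong as written, in the sense that it is incompatible with the inputs and sample size in its own paragraph. The relative effect implied on yearly risk is about twice as large (18.8%). On 3-year risk it is 16-19%, with HR about 0.79-0.83.

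The result rests on the plain reading of the mixture (19% AF in both arms, 13% untreated in control), constant yearly risks, full 3-year follow-up, and all detected AF carrying the treated risk, as the inputs have it. The contradiction does not depend on the choice of conversion; only the exact implied effect and power do.

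Replacing 9% with 19% would not by itself make the paragraph consistent. The stated 80% at 2718 is not reached under any conversion tried, and at 3262 it is reached only with 3 × yearly risk and no loss, which leaves nothing of the 20% allowance for dropout and treatment discontinuation.

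**What to change.** Delete the 9%. State instead the effect that the inputs imply: about 19% relative on yearly risk, 6.7% against 5.4% per year, about 3-4 points at 3 years. Say which measure each number is.

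Give the recalculated power for that effect beside it, at 2718 (about 53-73%) and at 3262 with no loss (about 61-80%), and name the conversion and formula used. Do not carry over the 80%. Then reconcile the effect, the Table 2 inputs and the 2718 with the appendix calculation, so that one set of assumptions produces all of them. If the appendix contains an assumption that the article omits, print it in Table 2.

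The cost is a short correction to the sample-size text, and to the SAP if it repeats the sentence, plus one re-run of the calculation. Endpoint, test and alpha are untouched. The stated sensitivity and power become less favourable, and the steering committee may then have to decide whether the recalculated power is acceptable.

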#### Recruitment

Patients will be screened and included during ischaemic stroke or TIA admissions in stroke units. Participating centres report at least 200 stroke/TIA admissions yearly. With the anticipated participation of 30 sites, they need to randomise 0.6 patients weekly during the 3 years of inclusion to fulfil the recruitment target of 3262 participants.

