**Methods and analysis:**

AF SPICE is a multicentre, national, investigator-initiated, randomised, parallel-group, register-based trial comparing extended ECG monitoring versus standard ECG monitoring in patients admitted with ischaemic stroke or TIA, with a composite endpoint of stroke, all-cause-mortality and intracerebral bleeding. Patients aged ≥70 years without previous AF will be randomised 1:1 to control (standard ECG monitoring) or intervention (extended ECG monitoring). In the control arm, patients will undergo 48±24 hours (ie, a range of 24–72 hours) of continuous ECG monitoring according to national recommendations. In the intervention arm, patients will undergo 14+14 days of continuous ECG monitoring 3 months apart using an ECG patch device, which will provide an easy-accessed, well-tolerated 14-day continuous ECG recording. All ECG patch recordings will be read in a core facility. In cases of AF detection, oral anticoagulation will be recommended if not contraindicated. A pilot phase has been concluded in 2022, which will transcend into the main trial during 2023–2026, including approximately 30 stroke units. The sample size was calculated to be 3262 patients. The primary outcome will be collected from register data during a 36-month follow-up.

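### The stated recruitment rate of 0.6 patients per site per week gives 2808 participants in 3 years from 30 sites, not the target of 3262, which needs about 0.70

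*Protocol article*

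**What the plan says.** The Sample size section arrives at the target in two steps. The calculation itself ends with "resulting in a sample size of 2718 for 3 years of fixed follow-up time after inclusion". The protocol then continues: "Adding 20% for participant dropouts and treatment discontinuation, a total sample size of 3262 is needed". That total is split equally between the two arms, 1631 in each.

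The Recruitment section turns the total into a workload for the sites. It begins "With the anticipated participation of 30 sites" and goes on to say that "they need to randomise 0.6 patients weekly during the 3 years of inclusion to fulfil the recruitment target of 3262 participants". One sentence therefore fixes four quantities: the number of sites, the weekly rate, the length of inclusion and the total.

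Two other places bear on the timetable. The abstract describes the "main trial during 2023–2026, including approximately 30 stroke units". The abstract and the Study setting section both say that a completed pilot passes into the main trial. Neither gives the number of pilot participants or says whether they count toward the target.

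**The concern.** Any three of the four quantities in the Recruitment sentence determine the fourth, so the sentence can be checked without outside information. The check fails. The rate presented as sufficient for 3262 does not produce 3262 from the stated sites in the stated time.

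What is at stake is feasibility and timing. The sentence tells the reader what each site has to deliver for the trial to reach its sample size, and it understates that workload. If sites deliver exactly the printed rate, either inclusion runs past the stated 3 years, and the end of the 36-month follow-up moves with it, or inclusion closes on time with fewer participants than the Sample size section requires.

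**Working it through.** **Inputs**

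- Sites: 30 (Recruitment; the abstract says approximately 30).
- Rate: 0.6 patients per week (Recruitment). This can only be a per-site figure, since 0.6 per week for the whole trial would give 0.6 x 156 = 94 patients.
- Inclusion: 3 years (Recruitment), which is 156 weeks at 52 weeks per year.
- Target: 3262 (Recruitment and Sample size).
- Size before the addition: 2718; addition: 20% (Sample size).

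**Step 1. The target.** 2718 x 1.20 = 3261.6, rounded up to 3262, and 2 x 1631 = 3262. The target follows from the 2718 as stated.

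**Step 2. The total that the stated rate delivers.** Total = sites x rate x weeks = 30 x 0.6 x 156 = 2808. The shortfall is 3262 - 2808 = 454, and 454/3262 = 13.9%. The stated figure is not reproduced.

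**Step 3. Rounding and the length of a year.** A rate printed as 0.6 could lie between 0.55 and 0.65.

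| Rate per site per week | Total at 52 weeks per year | Total at 52.18 weeks per year |
|---|---|---|
| 0.55 | 2574 | 2583 |
| 0.60 | 2808 | 2818 |
| 0.65 | 3042 | 3052 |
| 0.70 | 3276 | 3287 |

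No rate that rounds to 0.6 reaches 3262 under either convention. The smallest remaining gap at 52 weeks per year is 3262 - 3042 = 220.

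**Step 4. The rate that the target needs.** Rate = target/(sites x weeks) = 3262/(30 x 156) = 0.697 (0.695 at 52.18 weeks per year). This rounds to 0.7 and is 0.697/0.6 = 1.16 times the printed rate.

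**Step 5. A possible origin.** For the size before the addition, 2718/(30 x 156) = 0.581, which rounds to 0.6. The agreement is at one digit only, since 0.6 taken literally gives 2808 and not 2718 (2808/2718 = 1.033).

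**Step 6. What keeping 0.6 would mean.**

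- Longer inclusion: 3262/(30 x 0.6) = 181 weeks, and 181/52 = 3.5 years, which is 25 weeks or about 6 months more than stated.
- More sites over 3 years: 3262/(0.6 x 156) = 34.9, or about 35.
- Closing at 3 years with 2808: the planned allowance is 3262 - 2718 = 544 participants. What remains is 2808 - 2718 = 90, or 3.3% of 2718 instead of 20%. The part lost is 454/544 = 83%.

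**The case against.** The arithmetic is hard to dispute. The case on the other side concerns cause and consequence, and much of it stands.

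**Cause.** A reader might infer that the rate was worked out from 2718 and not updated when the 20% was added. The article does not say how 0.6 was obtained, and the match exists only after rounding. It remains a plausible explanation, and the error does not depend on it.

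**Monitoring.** A reader might infer that 0.6 is the yardstick by which the DSMB judges inclusion, so that a shortfall would pass unnoticed. The article does not support this. The Data monitoring committee section has the board report each year on cumulative inclusion and names no rate or threshold. The target of 3262 is stated in the abstract and in two later sections, so a running count against it would show the gap.

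**Size of the trial.** A reader might infer that the trial will end 14% too small and lose power. That assumes inclusion stops at 3 years whatever the count, which no section says. The sentence speaks of a target to be met, and if inclusion runs until it is met the effect is delay. The calendar years in the abstract might accommodate 3.5 years, although the Recruitment section says 3.

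**Pilot participants.** The wording on the pilot leaves open that its participants count toward the target. About 454 of them would close the gap at 0.6, or at least 220 if 0.6 is a rounded 0.65. No pilot number is given, however, and the Recruitment sentence presents the weekly rate as fulfilling the whole 3262.

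**Feasibility.** At the minimum of 200 admissions per year that centres report, 0.6 per week is 31 patients a year (16% of admissions) and 0.7 is 36 (18%). The judgement that the trial is feasible changes little.

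**Conclusion.** The point holds as a wrong stated figure. With 30 sites and 3 years of inclusion, 0.6 patients per site per week yields 2808 participants, 454 (14%) below the target. The rate needed is about 0.70. This is robust to rounding of the rate and to the number of weeks in a year. It rests on 0.6 being an average per site, on 30 sites contributing throughout the 3 years, and on no pilot participants being counted. The article states nothing that would relax these assumptions enough to close the gap.

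The consequence is limited. At the printed rate, the trial either needs about 6 more months of inclusion or, if closed at 3 years, keeps an allowance of about 3% for dropout and discontinuation where 20% was planned. The article does not settle which would happen. The sample size target, the significance level, the endpoint and the analysis are unaffected.

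**What to change.** Make the four figures in the Recruitment sentence agree, in one of three ways:

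- restate the rate as about 0.7 patients per site per week, with 30 sites and 3 years (30 x 0.7 x 156 = 3276);
- keep 0.6 and 30 sites, and state about 3.5 years of inclusion;
- keep 0.6 and 3 years, and state about 35 sites.

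If pilot participants count toward 3262, give their number, subtract it from the target and derive the rate from the remainder.

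The first option costs one corrected figure, plus telling sites that the expected rate is about 16% higher. The second moves the end of follow-up by about half a year, and the abstract's dates should be checked against it. The third requires about five more sites. None of them changes the sample size calculation or the analysis.
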